**V1: Baseline assessment and familiarisation with EMS**

During the first visit, the consent form, a spirometry test and a bleep fitness test will be completed. The aim of this session will also be for the patient to familiarise himself with the apparatus (how to use the electrical stimulator, how to stick the electrodes to the skin, how to control the stimulation intensity).

**V2: Autonomous use of EMS, measure of pain perceived and of muscle fatigue**

The aim of this visit is to ensure that the patient can carry out electrical muscle stimulation in autonomy so that he will be able to use the apparatus at home. A full stimulation session will be carried out during which the patient will progressively take charge of the session. During electrical muscle stimulation, symptoms will be monitored (pain perception). The strength of the quadriceps will be tested before and after the session in order to measure the muscular fatigue caused by an initial EMS session. Finally, body composition will be determined during the course of this visit.

**V3: Assessment of EMS progression. Measure of pain perceived and of muscle fatigue at EMS intensity used during the sessions at home.**

The aim of this visit is to measure the pain perceived during a session of electrical muscle stimulation carried out at the EMS intensity that was used during the sessions at home. At the start of the session, the intensity of the stimulation applied will be that reached during visit 2, in order to compare the pain perceived for a given intensity, after 7 days of using the apparatus. Next, the patient will be asked to increase the intensity up to the level reached at home in order for us to calculate the intensity increase delta between V2 and V3. Throughout the course of this EMS session, the cardio-respiratory response will be measured using a portable “metabograph” fitted with a telemetric system (Oxycon mobile, Viasys). Furthermore, a blood sample will be taken before and after the session in order to measure systemic inflammation and oxidative stress levels. Lastly, muscular strength will be measured in order to determine the fatigue induced by this session.

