**Details of the electrical muscle stimulation sessions**

General concept: Simultaneous muscular stimulation of both legs induced by an electric current conducted by two cutaneous electrodes. Throughout the session, a period of muscular contraction alternates with an “active” recovery period (stimulation frequency which favours local blood circulation). The stimulation intensity is progressively increased provided it is well tolerated by the patient.

Site: LAVAL hospital and at the patient’s home

**Visit 1: Initiation session:** presentation of the electrical muscle stimulation program, positioning of the electrodes and learning how to use the apparatus.

**Visit 2: Session to gain autonomy of use:** observation that the patient can satisfactorily carry out an EMS session autonomously.

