**At home: five EMS sessions carried out autonomously at home**

During the seven days separating visits V2 and V3, the patient will be required to carry out 5 sessions at home. He will be asked to increase the EMS intensity as much as he can throughout one session and from one session to another, whilst staying beneath his pain threshold. In other words, he will have to increase the intensity frequently in order to always be at the maximum bearable intensity. For each session, the patient will have to write down the initial and final intensities along with the level of pain perceived for each. Throughout the week, we will maintain contact by phone (one initial phone call the day of the first session at home and then according to the patient’s needs) in order to answer any questions and/or solve any potential technical difficulties.

**Visit 3: Training session,** session as carried out by the patient at home.

Electrode placement

**Three electrodes on each leg:** two electrodes (50*50 mm) are placed on the skin by the lateral and the medial vastus of the quadriceps + one electrode (50*90 mm, double outlet) placed horizontally towards the top of the thigh, beneath the groin.

**
[figure not shown]

[figure not shown]
**

*Electrode placement for thigh rehabilitation*

*In this picture, the electrodes placed at the upper thigh are smaller models which will be replaced by electrodes of larger calibre, positioned side by side lengthwise (59*90 mm)*

**Electrode placement will be standardised** so as to lie by the lateral and the medial vastus motor points. The motor points will be identified for each patient individually, using a **pen electrode** that helps determine motor pathways and points of emergence.

Program

**Intermittent frequencies**: contraction at 50 Hz / “active” muscle relaxation at 5 Hz

- - - contraction 7 sec / relaxation 10 sec

**Time to reach contraction**: 3 seconds / time to relaxation: 1 second. Considering that the contraction is incomplete during the first two seconds of the contraction process, the cycles are 30%.

**Pulse width** = 400 µm

**The intensity** at which the patient begins to feel contraction of his thigh muscle is defined as the initial intensity; it is then progressively increased in order to reach the maximal bearable intensity.

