**Objective #2**

Identify correlations between ∆Intensity (V3-V2) and the pain perceived during the initial session V2 (VAS reading for the intensity reached during V2) and between ∆I (V3-V2) and the change in pain perceived between V2 and V3 (VAS reading at equal intensity)

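### The V2–V3 pain change at equal intensity pairs a reading taken after a progressive build-up with one taken at session start, so it mixes session position with seven days of use

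*Protocol*

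**What the plan says.** **The analysis.** Under Analysis of the results, Objective #2 has two parts. One relates ∆Intensity to pain at V2, described as the "VAS reading for the intensity reached during V2". The other relates it to "the change in pain perceived between V2 and V3 (VAS reading at equal intensity".

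**How the V2 intensity is reached.** The general concept under Details of the electrical muscle stimulation sessions says: "The stimulation intensity is progressively increased provided it is well tolerated by the patient". The Program paragraph defines the initial intensity as the point where the patient begins to feel the thigh contract, and adds: "it is then progressively increased in order to reach the maximal bearable intensity". The V2 section says of pain only: "During electrical muscle stimulation, symptoms will be monitored (pain perception". It sets no time points.

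**How V3 starts.** The V3 section says: "At the start of the session, the intensity of the stimulation applied will be that reached during visit 2". The stated purpose is "in order to compare the pain perceived for a given intensity, after 7 days of using the apparatus". The patient then moves up to the level reached at home. Elsewhere, the Visit 3 line under Details of the sessions describes V3 as a "session as carried out by the patient at home".

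**Other pain data.** In each of the five home sessions the patient notes the initial and final intensities and the pain felt at each.

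**The concern.** A before-and-after comparison at a fixed stimulus isolates the effect of the intervening week only if the stimulus is delivered under the same conditions both times. Here the V2 reading belongs to a level that the patient has worked up to, while the V3 reading belongs to the same level applied at the outset.

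If pain at a given intensity depends on how long, or by what steps, the patient has been stimulated, the difference contains that dependence as well as the effect of the week. The specific hypothesis is that pain falls over sessions when stimulation is applied progressively, and the V3 start-of-session reading does not clearly meet that condition.

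At stake are the pain-change half of Objective #2 and any statement about a mean fall in pain at fixed intensity. The omission is one of measurement timing. If no reading is taken at a comparable point, no later analysis can supply it.

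**Working it through.** **The protocol's figures.** The only design figure is the sample size, 3 groups × 7 = 21, which reproduces. No alpha, power, VAS standard deviation or position effect is stated, so everything numerical below is illustrative.

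**Step 1: where each reading falls.**

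| | V2 | V3 |
|---|---|---|
| Intensity | Level reached at V2 | Same level |
| Route to it | Progressive increase from first felt contraction (Program; general concept) | Applied at session start (V3 section) |
| Time of VAS | Not stated; follows the increase, because it is the reading for the level reached | Start of session, before the move to the home level |

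No section matches session position, adds a start-of-session V2 reading at that level, or allows for position in the analysis.

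**Step 2: effect on the mean change.** Let T be the true seven-day change at equal intensity and equal session position. Let A be the VAS difference due to position alone (start of session minus after build-up). Then:

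observed change = T + A

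Results in VAS points, with T and A both assumed:

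| T | A = −1 | A = 0 | A = +1 | A = +2 |
|---|---|---|---|---|
| 0 | −1 | 0 | +1 | +2 |
| −1 | −2 | −1 | 0 | +1 |
| −2 | −3 | −2 | −1 | 0 |

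A positive A (accommodation during the V2 build-up) hides or reverses a fall. A negative A (fatigue or sensitisation by the time of the V2 reading) exaggerates or creates one.

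**Step 3: effect on the planned correlation.** If A is the same for every patient, the correlation with ∆Intensity does not change. If A varies between patients, independently of T and ∆Intensity, with k = SD(A)/SD(T):

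observed r = true r / √(1 + k²)

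Power, by Fisher's z with n = 21 and an assumed two-sided 0.05, is Φ(atanh(r) × √18 − 1.96). For an assumed true correlation of 0.60 in absolute value:

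| k | Observed r | Power |
|---|---|---|
| 0 | 0.60 | 0.84 |
| 0.5 | 0.60/√1.25 = 0.54 | 0.72 |
| 1.0 | 0.60/√2 = 0.42 | 0.49 |

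**Step 4: with matched positions.** A = 0, and the observed change equals T. No figure in the protocol changes.

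**The case against.** Several points on the other side stand.

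- **Timing is partly inferred.** The protocol gives no clock times for the V2 VAS, and the start of the V3 session could include a short ramp. The asymmetry follows from a progressive increase at one visit and a start-of-session application at the other, not from a timing table. This limits how firmly the size can be stated, and it is also a reason to define the measuring point.
- **Direction.** A reader might infer that the V3 start biases the estimated fall in pain downwards. The documents do not support that. They report no within-session accommodation of pain; it can only be guessed from the request to keep raising intensity during a home session. The secondary hypotheses expect muscular fatigue after stimulation, and if fatigue raised pain by the time of the V2 reading it would act the other way.
- **Correlations.** The stated analyses are regressions and correlations with ∆Intensity, so a shift common to all patients does no harm there.
- **Other pain data.** A reader might infer that this contrast is the protocol's only evidence on pain over sessions. It is not, because the home diary records pain too. Those scores are at changing intensities, however, and no listed objective uses them.
- **The two descriptions of V3.** A reader might infer a flat contradiction. The V3 section is the more specific text and can be read as governing, with the Visit 3 line as a short label. The wording still leaves room for two ways of starting V3.
- **Matching exact elapsed time.** Both sessions are planned at 30 minutes. If the V2 level is reached late, waiting equally long at V3 could crowd out the home-level stimulation whose cardio-respiratory, strength and blood measures serve Objectives #1, #4 and #5.

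None of this removes the mismatch between the two readings.

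**Conclusion.** The point holds in a limited form and deserves a protocol change. As written, the V2–V3 pain change cannot be attributed to seven days of use alone, because the two readings sit at different points of the session.

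The size and sign of the distortion are unknown. Under the assumed range, an offset of one point is enough to cancel a true 1-point fall or to double it. An assumed correlation of 0.60 would drop to between 0.54 and 0.42 only if the offset varies between patients with 0.5 to 1.0 times the standard deviation of the true change, and independently of that change and of ∆Intensity.

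The scope is narrow: the pain-change half of Objective #2 and the mean fall in pain at fixed intensity, for which this is the only comparison in the stated analysis. A reader might extend the criticism to tolerance as a whole. That would go too far, because ∆Intensity and its correlation with V2 pain do not depend on when the V3 VAS is taken, and the tolerance criterion of pain at a given intensity need not mean this change.

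**What to change.** 1. Reconcile the V3 section, which starts at the V2 level, with the Visit 3 line and the Program paragraph, which describe a session as at home and an initial intensity at first felt contraction. This review does not say which start is right.
2. At V2, record VAS together with intensity and time during the build-up.
3. At V3, take the paired VAS at a common intensity and a comparable point of the build-up, before the move to the home level. Do not require the same full elapsed time.
4. Define the Objective #2 pain change from that matched pair only.
5. If the V3 start-of-session reading is kept, report it separately and do not attribute its difference from V2 to training alone.

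The cost is protocol wording, a few extra VAS readings and time stamps in sessions already held with pain monitoring already planned, and slightly less V3 time at the home level.

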Nevertheless, our experience (ESTIM protocol, CER #20105) shows that some patients experience difficulties in increasing the intensity of stimulation, even after several weeks of training thus limiting the treatment’s effect [17]. However, the cardio-respiratory response of a COPD patient during a session of electrical muscle stimulation has never been described. Theurel’s study, carried out with healthy subjects, suggests that minute ventilation increases significantly more when the intensity of the electric stimulation is increased than during voluntary exercise of equal intensity. Minute ventilation may increase to 10L/min (23 ± 4 vs 13 ± 3 L/min at rest) when the intensity reaches 50% of the maximal voluntary contraction [18]. Furthermore, this study shows that oxygen consumption and heart rate increase with time and intensity during a session of electrical muscle stimulation. These factors could limit the ability for patients to tolerate electrical muscle stimulation in the same way as a decrease in oxygen saturation, and are worth investigating. What is more, the abilities to produce and to tolerate muscular contraction at a given stimulation intensity vary greatly for one individual and between individuals [19, 20] particularly for thinner individuals [14]. Body composition, especially at the site of stimulation, could influence the transmission of the electric stimulation and therefore could be partly responsible for intolerance to electrical muscle stimulation. Finally, there is currently no data concerning induced muscular fatigue and the metabolic expenditure associated with a complete session of electrical muscle stimulation in COPD patients. This type of information could help determine the minimum delay to respect between two sessions of electrical muscle stimulation in order to allow optimal muscular recovery in patients and improve long-term tolerance to a course of electrical muscle stimulation.

We therefore propose to evaluate COPD patient tolerance to electrical muscle stimulation together with the cardio-respiratory response, the symptoms linked to exercise (daily exercise, maximal exercise) and felt during the electrical muscle stimulation itself (pain perception), body composition, and the muscle fatigue which follows a stimulation session.

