**Specific hypotheses:**

A large increase in ventilation, an acceleration in heart rate and/or a fall in arterial oxygen saturation during electrical muscle stimulation decreases patient tolerance to EMS.

Excessive pain perception lowers tolerance to electrical muscle stimulation. Pain perception diminishes over the course of several EMS sessions when electrical muscle stimulation is applied progressively.

Low body fat around the quadriceps is associated with increased pain perception during a session of electrical muscle stimulation and is therefore associated with lower tolerance to this training modality.

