***Bleep fitness test***

In order to quantify the patient’s cardio-respiratory response to maximum effort, patients will undergo an incremental bleep fitness test as frequently carried out in our lab (Pepin et al. 2005). This test uses a portable “metabograph” fitted with a telemetric system (Oxycon mobile, Viasys) to measure ventilation, oxygen consumption, heart rate and saturation throughout the exercise. Physiological values measured during a session of electrical muscle stimulation can therefore be compared to the maximal values measured during this test. Furthermore, this test will allow us to characterise the patients’ physical condition. Fifteen minutes before this test an electrocardiogram (ECG) at rest will be carried out.

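### Heart rate, ventilation and saturation under EMS are first recorded at V3, after the intensity change they are meant to explain, and Objective #1 does not say at which intensity they are read

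*Protocol*

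**What the plan says.** **When the response is recorded.** For the V2 stimulation session the Study schedule says "During electrical muscle stimulation, symptoms will be monitored (pain perception" and closes the bracket there; no cardio-respiratory variable is listed. For V3 it says "Throughout the course of this EMS session, the cardio-respiratory response will be measured", with the portable metabolic system. The visit flowchart agrees: that system appears with EMS under Visit 3 only. The home log holds intensities and pain. The V1 fitness test does measure ventilation, heart rate and saturation, but at maximal effort without EMS, and it supplies the maximum values.

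**How V3 runs.** "At the start of the session, the intensity of the stimulation applied will be that reached during visit 2". "Next, the patient will be asked to increase the intensity up to the level reached at home". The second step gives ∆Intensity (V3-V2).

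**What is analysed.** Objective #1 correlates ∆Intensity with the cardio-respiratory response, raw and as a percentage of maximum, without naming the intensity at which it is read. Analysis of the results names simple and multiple regression. Objective #2 uses pain at the V2 intensity and a pain comparison at equal intensity.

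**What is expected.** The Specific hypotheses are directional: a large rise in ventilation, a faster heart rate or "a fall in arterial oxygen saturation during electrical muscle stimulation decreases patient tolerance to EMS". The Introduction, citing healthy subjects, says that "oxygen consumption and heart rate increase with time and intensity during a session of electrical muscle stimulation", and that "minute ventilation increases significantly more when the intensity of the electric stimulation is increased" than in voluntary exercise of equal intensity. It makes no such statement for saturation.

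**The concern.** There are two separate problems.

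*Order in time.* The hypothesis treats the response as the cause and poor progress as the effect, yet the first response is recorded after the progress. The section on EMS implementation counts V3 as the seventh session. The six before it (V2 and five at home) have no cardio-respiratory recording. An analysis plan can choose among the V3 readings but cannot supply one from V2.

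*Coupling.* The home-intensity reading is made at V2 intensity + ∆Intensity. If the response rises with intensity, patients who progressed most show the largest response for that reason alone. The correlation is pushed upward while the hypothesis predicts a negative one, so a real effect could be masked or reversed. Expressing values as a percentage of maximum does not help, because only the denominator comes from V1.

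**Working it through.** **Inputs from the protocol.** n = 3 × 7 = 21. ∆ = I3 − I2, where I2 and I3 are the V2 and V3 (home) intensities. The protocol gives no SDs, correlations, alpha or power.

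**Assumptions.** Two-sided 5% tests; equal SDs of I2 and I3; corr(I2, I3) = ρ of 0.5 or 0.8; response = b × intensity + u, where u is the patient's own reactivity; c = corr(response, intensity), with b = c/√(1 − c²). Critical |r| is 0.433 unadjusted (19 df) and 0.444 with one covariate (18 df). Rejection rates are from simulation, 20,000 runs per setting.

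**1. No true effect.** For the unadjusted home-intensity reading, cov(bI3 + u, I3 − I2) = b(1 − ρ) and var(∆) = 2(1 − ρ), so r = c√((1 − ρ)/2).
- c = 0.7, ρ = 0.5: 0.7 × 0.50 = +0.35
- c = 0.3, ρ = 0.8: 0.3 × 0.316 = +0.09
- c = 0.1: +0.03 to +0.05

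The V2-intensity reading has the same size with a minus sign, because I2 enters ∆ negatively.

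| Reading and adjustment (c = 0.3 to 0.7) | Mean r | Significant in the direction of the bias (nominal 2.5%) |
|---|---|---|
| Home intensity, none | +0.09 to +0.34 | 6–35%, against the hypothesis |
| Home intensity, for I2 | +0.18 to +0.64 | 12–91%, against the hypothesis |
| Home intensity, for I3 | 0.00 | 2.3–2.7% per side (no bias) |
| V2 intensity, none | −0.09 to −0.34 | 6–35%, false support |
| V2 intensity, for I2 | 0.00 | 2.3–2.5% (no bias) |

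At c = 0.1 the first row falls to about 4%. These are not bounds. If I3 has 1.5 times the SD of I2, the unadjusted home-intensity r is +0.31 to +0.62; the adjusted V2-intensity reading stays at 0.00.

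Each reading therefore needs the intensity at which it was taken as its covariate.

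**2. True effect, assumed partial r of −0.5 (g = 0.5).**
- Home intensity, unadjusted: found in 1–44% (c = 0.3 to 0.7).
- Home intensity, adjusted for I3: partial r = −gρ/√(1 − g²(1 − ρ²)). For ρ = 0.5 this is −0.25/√0.8125 = −0.28; for ρ = 0.8 it is −0.40/√0.91 = −0.42. Power is about 22% to 47%. Once I3 is held fixed, ∆ varies only through I2, so much of the signal is lost.
- V2 intensity, adjusted for I2: partial r = −0.50, power about 64%. This is a noise-free ceiling. With reliability q the partial r is −0.5√q: −0.42 at q = 0.7 (about 47%) and −0.35 at q = 0.5 (about 34%). Noise would lower the power of the home-intensity reading too.

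**3. V2 reading or V3 opening?** Without adaptation over the week the two are identical in this model. If the fall in response over the week correlates 0.1 to 0.4 with progress (an assumption), the adjusted V3-opening reading gives mean r of −0.10 to −0.39 and false support in 6–44%; the adjusted V2 reading stays at 2.3–2.8%.

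**The case against.** The strongest reply is that the study is observational and its first specific objective asks only whether the responses go together with intolerance. A concurrent V3 reading can answer that. The recorder runs throughout V3, which opens at the V2 intensity, so an equal-intensity reading of all three variables will exist. Choosing the window and covariate is ordinary analysis-plan work. All of this stands. What remains is that the Specific hypotheses claim an effect, for which order in time matters, and that no later plan can create a V2 reading.

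A reader might infer that the home-intensity reading is beyond repair. It is not: adjusting for V3 intensity removes the null bias, at a cost in power.

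A reader might also infer that the V3 opening is known to be spoiled by the training week. The protocol expects a decline over sessions for pain only, and the adaptation correlation above is assumed. The opening also comes early in a session, while the cited response rises with time as well, so its window must be fixed.

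The coupling is itself an extrapolation: the cited response comes from healthy subjects, and the Introduction stresses wide variation between individuals at a given intensity. A weak correlation (c = 0.1) leaves little bias, and for saturation no relation to intensity is stated.

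Finally, unmonitored home use might be read as a safety failing. The documents do not support that. There is a monitored maximal test, and for the resting tracing, "Fifteen minutes before this test an electrocardiogram (ECG) at rest will be carried out". At home there are a pain ceiling and phone contact, and no cardio-respiratory harm is reported.

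**Conclusion.** The point holds as a cheap improvement. It is certain from the text that no cardio-respiratory response under EMS is recorded before V3 and that Objective #1 does not fix the intensity of the reading. The upward push on an unadjusted home-intensity correlation follows for any variable that rises with intensity; the Introduction says this of ventilation and heart rate. Its size rests on assumed SDs and correlations: about 4% to 35% wrong-direction significance against 2.5%, at n = 21 with equal SDs. The documents do not show that Objective #1 is unanswerable as it stands, nor that a V2 reading would guarantee good power. The gain is a correct time order for heart rate and saturation, and a defined, unbiased equal-intensity predictor for all three variables.

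**What to change.** (a) During the existing V2 session, record heart rate and saturation by pulse oximeter, together with the intensity in use and elapsed time.

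(b) In Objective #1, use the response at the V2 intensity as the predictor of ∆Intensity: the V2 reading for heart rate and saturation, and a fixed window at the opening of V3 for ventilation. Adjust for V2 intensity in the multiple regression already named, and state that the ventilation result is post-training.

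(c) Report the home-intensity V3 response descriptively. If it is correlated with ∆Intensity, adjust it for V3 intensity, not V2 intensity.

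**Cost.** A short amendment, no new visit, a few minutes of set-up at V2, and one residual degree of freedom (19 to 18). The number of coefficients stays at six: 2 variables × 2 scales from V2 plus 1 × 2 from V3, against 3 × 2 now.

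**Limits.** Ventilation still has no pre-training reading, and V2 heart rate as a percentage of maximum would set an oximeter value against a maximum from the portable metabolic system. Using that system at V2 would solve both, but it adds equipment to a session meant to teach autonomy and might affect V2 pain and intensity, so it should stay optional.
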